### MRI interpretation

All MR scans will be prospectively read by two independent radiologists, blinded for each other's findings, US and CT results. These selected radiologists will be trained to adequately appraise the MR scan for presence or absence of appendicitis. Their training consists of 102 abdominal MR scans in patients presenting previously with clinically suspected appendicitis in one of the participating institutions (Medical Center Alkmaar). The MRI observers will document imaging findings in the on line CRF as described earlier for US and CT. Afterwards; all MRI examinations will be scrutinized by central reading by a MRI expert committee with the same clinical information as the initial MRI readers to establish a reference of optimal MRI accuracy for comparison with clinical practice MRI accuracy.

### Patient management

Patients will be managed based on the US and CT findings. MRI will not be used for management, except in equivocal findings at US and CT, or in case of other clinically important findings at MRI that were undetected at US and CT.

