**Methods/Design:**

Eligible for this study are consecutive patients presenting with clinically suspected appendicitis at the emergency department in six centers. All patients will undergo imaging according to the Dutch guideline for acute appendicitis: initial ultrasonography in all and subsequent CT whenever US does not confirm acute appendicitis. Then MRI is performed in all patients, but the results are not used for patient management. A final diagnosis assigned by an expert panel, based on all available information including 3-months follow-up, except MRI findings, is used as the reference standard in estimating accuracy. We will calculate the sensitivity, specificity, predictive values and inter-observer agreement of MRI, and aim to include 230 patients. Patient acceptance and total imaging costs will also be evaluated.

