### Reference standard

An expert panel consisting of two surgeons and a radiologist will assign a final diagnosis after a follow-up period of 3 months, based on all available information: clinical information, imaging findings (except MRI findings), surgery, pathology and follow up. General practitioners will be contacted to assess whether patients had an appendectomy in another hospital, or an alternative diagnosis assigned. The flowchart in figure 1 demonstrates the complete clinical pathway of included patients in the OPTIMAP study.

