### Data Analysis

Data analysis primarily will focus on the diagnostic accuracy of MRI in correctly identifying patients with appendicitis. Sensitivity, specificity, positive and negative predictive value of MRI in detecting acute appendicitis will be calculated with corresponding 95% confidence intervals, by comparing the results of MRI, as read by trained radiologists and the MRI expert panel, with the final diagnosis assigned by the expert panel. In addition, the accuracy of the following scenarios will be estimated: (1) Clinical evaluation without imaging, (2) US in all patients followed by CT after a non diagnostic US, (2) US only, (3) MRI only, (4) US followed by MRI after a non diagnostic US. A gain in diagnostic value of strategies using two tests will be evaluated using the likelihood ratio based method proposed by McAskill and colleagues [10]. Next, we will evaluate the diagnostic performance of stratified imaging strategies taking into account patient characteristics (e.g. age, gender) and presentation features (e.g. duration of complaints). We will also investigate accuracy modifiers, such as body mass index and gender, which are known to influence the diagnostic performance of some imaging modalities.

For the cost evaluation, we will estimate and compare the total imaging costs for each imaging strategy. Standard unit prices will be used for all imaging modalities. Total imaging costs in multi-modality strategies will be driven by the positivity rate of the first imaging procedure.

To evaluate inter-observer agreement we will calculate percentage agreement and kappa values for the diagnosis of appendicitis in MRI between observer 1 en 2 (clinical practice reading) en central reading. Effects of reader experience will be evaluated by comparing the accuracy of local reading (single observer) to the accuracy of the expert central reading.

We will evaluate patient acceptance of MRI in comparison to standard imaging practice as documented in the Dutch guidelines. For each examination participants are invited to rate their experience (including burden, discomfort and pain) using five-point Likert scales (none, mild, moderate, severe, extreme). Differences between US, CT and MRI will be tested for statistical significance.

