### Sample size calculation

We anticipate an MRI sensitivity of 90% and specificity of 95%, based on accuracy results in published series of primarily pregnant women [11]. Approximately 60% of patients with suspected appendicitis are expected to have a final diagnosis of appendicitis, based on the findings in the OPTIMA trial, which had comparable inclusion criteria and ran in similar hospitals [12]. To obtain sensitivity and specificity estimates with 95% confidence intervals not exceeding 10%, a study group of 230 patients is required. Of the 230 patients, 138 are anticipated to have acute appendicitis (60%), while MRI will correctly identify appendicitis in 124 (sensitivity 90%; 95% CI 84% to 94%) and correctly exclude appendicitis in 95 (specificity 95%; 95% CI 88% to 98%).

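### The abstract says MRI never guides management but the methods allow two exceptions, and in those patients the panel's reference diagnosis is not fully independent of MRI

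*Protocol article*

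**What the plan says.** The Methods/Design part of the abstract is unconditional: "Then MRI is performed in all patients, but the results are not used for patient management".

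The Patient management section makes ultrasonography (US) and CT the basis of care and then opens two exceptions for MRI. The first is stated as "MRI will not be used for management, except in equivocal findings at US and CT". The second reads "or in case of other clinically important findings at MRI that were undetected at US and CT".

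Under Reference standard, a panel of two surgeons and a radiologist "will assign a final diagnosis after a follow-up period of 3 months". It works "based on all available information: clinical information, imaging findings (except MRI findings), surgery, pathology and follow up", and general practitioners are asked about an appendectomy elsewhere or another diagnosis. Under Data Analysis, sensitivity, specificity and predictive values of MRI come from comparing its readings "with the final diagnosis assigned by the expert panel".

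**The concern.** A reader of the abstract would conclude that the patient's course, and so the reference diagnosis, cannot depend on MRI. The methods do not support that. Where an exception applies, the MRI result can contribute to the choice between operating and observing. That choice determines whether the panel receives a pathology report or only three months of clinical course. The panel does not see the MRI report, but it does see what followed from it.

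This is differential verification linked to the index test. It touches only the excepted patients, but the first group of these, with equivocal US and CT, is the one in which an additional test would matter most. A larger sample does not reduce an error of this kind.

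**Working it through.** **1. The wording.** The abstract states no exception and the methods state two. Both are current text, and they cannot both describe the same conduct.

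**2. What happens to an MRI error in an excepted patient.**

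- *False-positive MRI, patient operated on.* Pathology goes to the panel and normally shows a normal appendix. The case is scored as a false positive, with no gain for MRI.
- *False-negative MRI, patient observed, appendicitis declares itself.* Follow-up or the general-practitioner check normally reveals it. The case is scored as a false negative, with no gain for MRI.
- *False-negative MRI, patient observed, appendicitis resolves unrecognised.* There is no histology and the follow-up is uneventful. The case is scored as a true negative, which favours MRI.

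The third path is the main upward route.

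**3. The plan's own figures.** Inputs from Sample size calculation: sensitivity 90%, specificity 95%, prevalence 60%. Taking the 10% limit as the full width of the 95% interval (half-width 0.05):

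- patients with appendicitis: 1.96² × 0.90 × 0.10 / 0.05² = 138.3
- total: 138.3 / 0.60 = 230.5, which reproduces 230
- expected true positives: 0.90 × 138 = 124.2; false negatives: 13.8
- patients without appendicitis: 230 − 138 = 92; expected true negatives: 0.95 × 92 = 87.4; false positives: 4.6

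The section gives 95 patients as correctly excluded, which exceeds the 92 available. The steps below use 92.

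**4. Size, on assumed inputs.** The documents do not give the share of patients with equivocal US and CT. Let r be the number of missed appendicitis cases relabelled as no appendicitis. Then

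- apparent sensitivity = 124.2 / (138 − r)
- apparent specificity = (87.4 + r) / (92 + r)

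Assume 10% equivocal (23 patients), MRI wrong in 20% of them (4.6), and half of those errors relabelled, all of them false negatives: r = 2.3.

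- sensitivity: 124.2 / 135.7 = 91.5%, against 90.0%
- specificity: 89.7 / 94.3 = 95.1%, against 95.0%

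Varying one assumption at a time:

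| Equivocal (assumed) | MRI errors there relabelled (assumed) | r | Apparent sensitivity |
|---|---|---|---|
| 2% | half | 0.46 | 90.3% |
| 5% | half | 1.15 | 90.8% |
| 10% | one quarter | 1.15 | 90.8% |
| 10% | half | 2.3 | 91.5% |
| 20% | half | 4.6 | 93.1% |

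**5. A second parameterisation.** Set MRI sensitivity within the equivocal group directly, with 90% elsewhere. Take 12% equivocal. That is the CT failure rate in Background, used only as a point in the range and not as an estimate of the equivocal share.

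- Sensitivity 90% in the group: missed cases 138 × 0.12 × 0.10 = 1.66. With half relabelled, 124.2 / (138 − 0.83) = 90.5%, against a true 90.0%.
- Sensitivity 70% in the group: true overall sensitivity 0.88 × 0.90 + 0.12 × 0.70 = 87.6%, or 120.9 true positives; missed cases in the group 138 × 0.12 × 0.30 = 4.97. With half relabelled, 120.9 / (138 − 2.48) = 89.2%.

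These shifts are 0.5 and 1.6 points, the same order as in step 4.

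**The case against.** The strongest reply is that MRI enters management only by exception, that the methods disclose this openly, and that the reference standard has real safeguards: pathology after surgery, three months of follow-up and the general-practitioner check. All of that stands, and it confines the problem to the third path in the working. The second exception may also largely concern diagnoses other than appendicitis.

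The illustration is generous as well. If the 4.6 assumed errors split as the plan's expected errors do (13.8 false negatives to 4.6 false positives), 3.45 of them are missed cases. Relabelling 2.3 then means that two thirds of the missed appendicitis resolves unnoticed. Even so, the shift is 1.5 points, well inside the planned interval of 84% to 94%.

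Four stronger readings are tempting, and the documents do not support them:

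- *A reader might infer that the panel's diagnosis simply follows MRI in these patients.* With 30% equivocal and MRI there only 70%/80% accurate (both assumed), complete dependence would inflate sensitivity and specificity by 8.6 and 6.2 points. Pathology and follow-up rule out complete dependence as a description of this design.
- *A reader might infer that surgery after equivocal US and CT reveals the MRI result.* The text permits use of MRI but does not say that MRI alone decides. Clinical findings can also lead to surgery.
- *A reader might infer that the US-then-CT scenario is scored on a diagnosis made after MRI.* Nothing says so, and the Standard care section has US and CT readings recorded separately.
- *A reader might treat the lack of a described analysis for these patients as a defect.* A condensed article may leave that to the full protocol or analysis plan.

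What remains is that the abstract asserts an independence which the methods do not provide.

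**Conclusion.** The point holds in limited form. The contradiction between the abstract and Patient management is certain. It is also clear from the text that, in the excepted patients, the reference standard is not fully independent of MRI. An upward bias in sensitivity is possible through MRI-negative equivocal patients whose appendicitis resolves unrecognised. It is not established as a fact about the whole study, and specificity is barely affected by this path.

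The size cannot be derived from the documents. It is 1.5 points of sensitivity in the 10% / 20% / half illustration, and near zero if equivocal patients are few or follow-up finds most missed cases. All three of those inputs are assumed.

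**What to change.** 1. Correct the abstract sentence so that it and Patient management state the same rule. Which rule applies is for the investigators.
2. Flag in the case record form (CRF), at the time of care, every patient whose management used MRI. This may not be recoverable later.
3. Report the number flagged, and whether each was verified by histology or by follow-up.
4. Score the US and US-then-CT scenarios on the readings already recorded under Standard care, entered before MRI is disclosed. A time stamp helps, because Rationale for design lets the order of CT and MRI vary.
5. Keep flagged patients in the main estimate. Add a worst-case sensitivity analysis in which each flagged patient without histology is scored against MRI. This is a bound, not an estimate.
6. An analysis excluding flagged patients may be shown beside it. It cannot stand alone as the correction, because it removes the hardest cases and can itself raise apparent accuracy.

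The cost is one time-stamped CRF flag, one or two sensitivity analyses and one corrected sentence. The sample size of 230 is unchanged.

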### Reference standard

An expert panel consisting of two surgeons and a radiologist will assign a final diagnosis after a follow-up period of 3 months, based on all available information: clinical information, imaging findings (except MRI findings), surgery, pathology and follow up. General practitioners will be contacted to assess whether patients had an appendectomy in another hospital, or an alternative diagnosis assigned. The flowchart in figure 1 demonstrates the complete clinical pathway of included patients in the OPTIMAP study.

**Figure 1 F1:**
[figure not shown]
The OPTIMAP study flowchart.

### Data Analysis

Data analysis primarily will focus on the diagnostic accuracy of MRI in correctly identifying patients with appendicitis. Sensitivity, specificity, positive and negative predictive value of MRI in detecting acute appendicitis will be calculated with corresponding 95% confidence intervals, by comparing the results of MRI, as read by trained radiologists and the MRI expert panel, with the final diagnosis assigned by the expert panel. In addition, the accuracy of the following scenarios will be estimated: (1) Clinical evaluation without imaging, (2) US in all patients followed by CT after a non diagnostic US, (2) US only, (3) MRI only, (4) US followed by MRI after a non diagnostic US. A gain in diagnostic value of strategies using two tests will be evaluated using the likelihood ratio based method proposed by McAskill and colleagues [10]. Next, we will evaluate the diagnostic performance of stratified imaging strategies taking into account patient characteristics (e.g. age, gender) and presentation features (e.g. duration of complaints). We will also investigate accuracy modifiers, such as body mass index and gender, which are known to influence the diagnostic performance of some imaging modalities.

For the cost evaluation, we will estimate and compare the total imaging costs for each imaging strategy. Standard unit prices will be used for all imaging modalities. Total imaging costs in multi-modality strategies will be driven by the positivity rate of the first imaging procedure.

To evaluate inter-observer agreement we will calculate percentage agreement and kappa values for the diagnosis of appendicitis in MRI between observer 1 en 2 (clinical practice reading) en central reading. Effects of reader experience will be evaluated by comparing the accuracy of local reading (single observer) to the accuracy of the expert central reading.

We will evaluate patient acceptance of MRI in comparison to standard imaging practice as documented in the Dutch guidelines. For each examination participants are invited to rate their experience (including burden, discomfort and pain) using five-point Likert scales (none, mild, moderate, severe, extreme). Differences between US, CT and MRI will be tested for statistical significance.

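### The reader-experience comparison sets one local observer against a later committee reading, so a difference cannot be attributed to experience

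*Protocol article*

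**What the plan says.** Three kinds of MRI reading are described in the protocol article.

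- **Local readings (MRI interpretation).** "All MR scans will be prospectively read by two independent radiologists", each blinded to the other and to ultrasonography and CT. On preparation: "Their training consists of 102 abdominal MR scans in patients presenting previously with clinically suspected appendicitis".
- **Central reading (MRI interpretation).** After the local readings, "all MRI examinations will be scrutinized by central reading by a MRI expert committee with the same clinical information as the initial MRI readers". Its stated purpose is "to establish a reference of optimal MRI accuracy for comparison with clinical practice MRI accuracy".
- **Use of the readings (Data Analysis).** Accuracy is calculated for MRI "as read by trained radiologists and the MRI expert panel". Percentage agreement and kappa are calculated "between observer 1 en 2 (clinical practice reading) en central reading". The next sentence plans to evaluate the effect of reader experience by "comparing the accuracy of local reading (single observer) to the accuracy of the expert central reading".

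The article does not describe individual expert readings, the size of the committee, or how the committee arrives at its reading. It does not say which of the two local readers is the single observer, or whether each is compared in turn.

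**The concern.** A comparison meant to isolate experience should hold the other features of the reading fixed. Clinical information is held fixed by design. Reading format is not: one side is an individual, the other a committee. Timing also differs, because local readings are prospective and the central reading follows. Since no individual expert readings are described, the planned data cannot separate expertise from group reading.

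The two sections also give one comparison two meanings. MRI interpretation treats it as best achievable against everyday accuracy, which the data can answer. Data Analysis presents it as an experience effect, which they cannot.

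A smaller point concerns precision. The agreement sentence treats observers 1 and 2 together as the clinical-practice reading, while the following sentence reduces local reading to one observer. Taken literally, half of the local readings are left out of this contrast.

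At stake is the interpretation of a secondary result. A gap between committee and local reading could be reported as evidence that more reader training or experience would close it, when part of the gap may come from reading as a group.

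**Working it through.** **1. The plan's own figures, to see whether they depend on this contrast.** Inputs from Sample size calculation: sensitivity 0.90, specificity 0.95, prevalence 0.60, 95% interval not exceeding 10% (total width, so half-width 0.05).

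- Sensitivity: n = 1.96² × 0.90 × 0.10 / 0.05² = 138.3, so 139 with appendicitis; 139 / 0.60 = 232, against 230 stated.
- Specificity: n = 1.96² × 0.95 × 0.05 / 0.05² = 73 without appendicitis; 73 / 0.40 = 183. Sensitivity therefore drives the total.
- Wilson interval for 124/138: 83.7% to 93.9% (stated 84% to 94%).
- Specificity on 230 × 0.40 = 92 patients, with 0.95 × 92 = 87 correct: Wilson interval 87.9% to 97.7% (stated 88% to 98%).

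The total and both intervals reproduce, and none of them uses the reader comparison.

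**2. What differs between the two sides of the contrast.**

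| Feature | Local reading | Central reading |
|---|---|---|
| Reader | trained radiologist | MRI expert |
| Format | single observer | committee |
| Timing | prospective | afterwards |
| Clinical information | same | same |

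At least two features besides experience change with it, so experience is not identifiable from the difference.

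**3. How large a pure format effect could be (illustration).** Assumptions, none from the article: a committee of three, decision by majority, each member with the same 90% sensitivity as a local reader, and within-patient correlation rho under a beta-binomial model. With s = 1/rho − 1, a = 0.90s and b = 0.10s, the majority sensitivity is P(at least 2 of 3 correct). For rho = 0 this is 0.9³ + 3 × 0.9² × 0.1 = 0.729 + 0.243 = 0.972. For rho = 0.5 (s = 1) it is (0.9 × 1.9 × 2.9 + 3 × 0.9 × 1.9 × 0.1) / (1 × 2 × 3) = (4.959 + 0.513) / 6 = 0.912.

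| rho | Majority sensitivity | Gain with equal experience |
|---|---|---|
| 0 | 97.2% | 7.2 points |
| 0.3 | 92.7% | 2.7 points |
| 0.5 | 91.2% | 1.2 points |
| 0.7 | 90.4% | 0.4 points |
| 0.9 | 90.0% | 0.0 points |

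**4. Precision of the paired difference with one or both local readings.** Let C be the committee result and L1, L2 the local results (correct = 1), with common variance V and common pairwise correlation rho (assumption).

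- One local reading: Var(C − L1) = 2V(1 − rho).
- Both: Var(C − (L1 + L2)/2) = V + V(1 + rho)/2 − 2·rho·V = 1.5V(1 − rho).
- Ratio: 1.5 / 2 = 0.75; width ratio √0.75 = 0.866, about 13% narrower. The factor (1 − rho) cancels, so this holds for any rho below 1.

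With V = 0.90 × 0.10 = 0.09 and 138 patients, the half-width is 1.96 × √(variance / 138). At rho = 0.5 that is 1.96 × √(0.09 / 138) = 5.0 points with one local reading and 1.96 × √(0.0675 / 138) = 4.3 points with both.

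If the local–local correlation (r) differs from the local–committee correlation (q), the variance ratio is 1 − (1 − r) / [4(1 − q)]. For r = 0.7, q = 0.5: 1 − 0.3/2 = 0.85, about 8% narrower. For r = 0.5, q = 0.7: 1 − 0.5/1.2 = 0.583, about 24% narrower.

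**The case against.** The strongest reply is that this is only a loose label. MRI interpretation already assigns the roles: the committee shows what MRI can achieve, the local readers show clinical practice. A reader who keeps that in mind will not be misled. Choice of local reader and handling of pairing are also matters that a condensed article may leave to the full protocol or analysis plan. The first part stands as a reason for low severity. It does not remove the point, because Data Analysis states an inferential purpose that the contrast cannot serve, and no later modelling choice separates experience from format without individual expert readings.

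The illustration in step 3 of the working deserves the same caution. The 7-point figure needs wholly independent readers; at correlations of 0.5 or more the gain is about 1 point or less, below the 4.3-point half-width calculated at 0.5. Committee size and decision rule are assumed.

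A reader might infer more than the article supports:

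- **That data are wasted.** Both local readings enter agreement and kappa, and the accuracy analysis speaks of radiologists in the plural. The single-observer wording may mean individual rather than group reading, with each observer taken in turn.
- **That precision will be overstated by pooling.** No section proposes treating 2 × 138 = 276 readings as independent.
- **That the most favourable reader can become the headline.** Data Analysis does not formally rank local and expert estimates, but MRI interpretation gives the committee its role as the optimal reference in advance.
- **That the confounding is with consensus reading, and the effect is probably overstated.** The article says committee, never consensus, and gives no basis for the size or direction of any format effect.

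**Conclusion.** The point holds in limited form. As defined, the contrast changes experience and reading format together, so it cannot support a statement about reader experience. It can support a statement about optimal versus clinical-practice MRI reading, which is the aim given in MRI interpretation. This follows from the text alone and needs no numerical assumption.

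The possible size of a format effect, 0 to 7 points of sensitivity, is illustrative only. The 13% gain in precision from using both local readings rests on equal variances and correlations across the three readings. It would move if the committee is more accurate or if the correlations differ, and it is a gain only if the single-observer wording means that one reading is left out.

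The analysis is secondary. The sample size of 230, its planned intervals and the accuracy estimates themselves are unaffected. Severity is low.

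**What to change.** In Data Analysis, replace the reader-experience sentence with a comparison of committee (optimal) reading against local clinical-practice reading, matching MRI interpretation, and state that no conclusion about reader experience will be drawn from it. Estimate the differences in sensitivity and specificity within patients, using both local readings for every patient, with confidence intervals clustered by patient (GEE or bootstrap).

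The cost is a change of wording, slightly more analysis work and a more modest conclusion. No new readings or patients are needed. If an experience effect is truly wanted, the alternative is blinded individual expert readings compared with individual local readings, which would require additional reading time.
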